#### Midwife interviews

About 15 midwives, including APPEAL champions will be invited to take part in one-to-one interviews during the initial implementation period. Interviews will explore their views on the training and the PFME intervention for women.

Following intervention implementation and after first postnatal contact (when midwives have advised women to expect a questionnaire), approximately 15 intervention and 15 control midwives will be invited for telephone interview. Midwives will be purposively selected to reflect team size and location to explore their views on current PFME provision, how and when they advise women on PFME as well as experiences of intervention implementation and trial process for intervention midwives.

#### Midwife intervention implementation

Via APPEAL midwife ‘champions’ for each cluster, the intervention community midwives will be invited to complete a short-questionnaire on barriers and facilitators to implementation of the APPEAL intervention.

Midwives participating in the process evaluation will be informed that they do not need to participate and if they do, but subsequently change their mind, they can request their data are not included in further analysis.

#### Sample size

The sample size was based on number of women and clusters needed to estimate the return rate of questionnaires (across trial arms) to an acceptable level of precision.

In an earlier pilot study to test data collection instruments, 243 questionnaires were received within the specified time from the 777 that were sent (31.3%, 95% CI 27.1 to 35.4%) across 14 midwife teams (average cluster size 55). The estimated ICC for this return rate is 0.007 (95% CI 0.0005 to 0.094) (estimated using the loneway command in Stata). We take the upper limit of the 95% CI as a conservative estimate of the ‘true’ return rate ICC and assume a value of 0.10 is reasonable.

Using this estimated ICC the width of the 95% confidence interval for different rates (e.g. return rate of questionnaires) can be estimated for a given sample size allowing for inflation of standard errors due to clustering (using a *t*-distribution with *K*-1 degrees of freedom where *K* is the number of clusters). To set a conservative upper bound on the required sample size we determine the widest 95% confidence interval for a given sample size, which will occur for a rate of 50%.

To reflect changes since the earlier pilot study in the number of midwifery teams and women cared for by the teams at participating sites, the overall sample size target is around 1400 (17 clusters of average size 82). We will be able to estimate the 95% confidence interval for the return rate to a maximum width of 17.2%.

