#### Randomisation

Midwifery community-based teams (clusters) will be randomised in a 1:1 ratio to standard care only or standard care plus intervention. A minimisation algorithm implemented in Microsoft Excel by the study statistician will be used to ensure approximate balance over the following variables:Midwifery team size defined by number of births (≤median monthly bookings vs >median monthly bookings)NHS maternity unit

A ‘random element’ will be included in the minimisation algorithm, so that each cluster has a probability of being randomised to the opposite treatment that they would have otherwise received.

Blinding of midwives providing care will not be possible due to the nature of the intervention. Women receiving antenatal care will not explicitly be blinded but the PFME support they experience will be the usual care provided by their midwives. Those responsible for conducting the trial analysis (but not the process evaluation) will be blind to allocation.

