#### Statistical analysis

A separate Statistical Analysis Plan will be produced to provide a comprehensive description of planned statistical analyses. We provide an overall summary of the proposed analysis here. The primary comparison groups are women in clusters allocated to intervention versus women in clusters allocated to standard care. In the first instance, all statistical analyses will be based on the intention to treat principle. Data analysis will be descriptive and mainly focus on confidence interval estimation, with no hypothesis testing. The assessment of missing data is an outcome measure of this feasibility and pilot trial.

We will report numbers contributing and numbers missing for all variables and descriptive statistics for all outcomes. Analysis methods will be chosen according to the data type of the outcome under investigation, in brief:Continuous endpoints (e.g. confidence scores elicited on a range 0**–**32): These data will be summarised using means and standard deviations, by armCategorical (dichotomous) endpoints (e.g. experience of UI in the past 4 weeks): The number of participants and percentages experiencing the event will be summarised by arm

For all total scores and dichotomous feasibility outcomes (e.g. proportion of women returning questionnaires) summary measures and 95% confidence intervals per trial arm will be estimated using a cluster level analysis, the *t*-distribution with df = *K*-1 and appropriate transformation where necessary (and weighting if there is variation in cluster sizes). This approach will appropriately allow for the clustered nature of the trial.

Quantitative data from intervention cluster midwives pre- and post-training session and intervention implementation questionnaires will be summarised using descriptive statistics and where appropriate inferential analysis undertaken using repeated measures statistical tests.

The final dataset will be available to members of the Trial Management and co-applicant group who need access to the data to undertake the final analyses.

Requests for access to data from the APPEAL trial should be addressed to [contact]. Anonymised individual participant data collected during the trial will be available with no end date. All proposals requesting data access will need to specify how the data will be used, and will need the approval of the trial management group prior to data release.

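### The stated maximum width of 17.2% for the return-rate interval is the equal-team-size result, although the plan expects team sizes to vary

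*Protocol article*

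**What the plan says.** The Sample size section of the protocol article bases the trial's size on how precisely the questionnaire return rate across arms can be estimated. The inputs are:

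- Size: "the overall sample size target is around 1400 (17 clusters of average size 82").
- ICC: the earlier pilot study gave this: "The estimated ICC for this return rate is 0.007 (95% CI 0.0005 to 0.094"). For planning, the authors take the upper limit and "assume a value of 0.10 is reasonable".
- Rate: "we determine the widest 95% confidence interval for a given sample size, which will occur for a rate of 50" per cent.
- Reference distribution: "using a *t*-distribution with *K*-1 degrees of freedom where *K* is the number of clusters".

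The result is: "We will be able to estimate the 95% confidence interval for the return rate to a maximum width of 17.2" per cent. The section says that standard errors are inflated for clustering. It mentions no allowance for unequal team sizes.

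Two other sections treat team size as variable. Under Randomisation, the first minimisation variable is "Midwifery team size defined by number of births", split at the median of monthly bookings. Under Statistical analysis, the cluster-level intervals per trial arm use a t-distribution, with transformation where needed "and weighting if there is variation in cluster sizes". The article gives neither the spread of team sizes nor the type of weight.

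**The concern.** A design effect computed from the average cluster size alone is exact only when all clusters are the same size. When sizes differ and each cluster counts in proportion to its size, which is what the simple percentage of women returning a questionnaire amounts to, the large clusters dominate and the variance rises. A width that already uses up the equal-size design effect is then not an upper limit, even at the rate and ICC chosen to be conservative.

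The return rate is the basis of the sample size and the first feasibility outcome listed. This width is the only planned precision figure in the article, so a reader will take it as what the trial can be relied on to deliver.

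**Working it through.** **Inputs from the Sample size section.** K = 17 teams, mean size m = 82, n = 17 × 82 = 1,394, ICC = 0.10, p = 0.50, t(0.975; 16 df) = 2.120.

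**Step 1: reproduce the stated figure.**

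- Design effect with equal teams: 1 + (82 − 1) × 0.10 = 9.1.
- Full width: 2 × 2.120 × √(0.25 × 9.1 / 1,394) = 17.13%.
- With n = 1,400 it is 17.09%. With the approximation 1 + 82 × 0.10 = 9.2 it is 17.22%.
- A normal quantile gives 15.8%, so the t quantile was used, as stated.

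The stated 17.2% is therefore the equal-team result.

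**Step 2: allow for unequal teams, with weights proportional to size.** Design effect = 1 + [(1 + CV²) × 82 − 1] × 0.10. The CV is an assumption, shown as a range.

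| CV of team size | Design effect | Full width |
|---|---|---|
| 0 | 9.10 | 17.1% |
| 0.1 | 9.18 | 17.2% |
| 0.3 | 9.84 | 17.8% |
| 0.5 | 11.15 | 19.0% |
| 0.7 | 13.12 | 20.6% |

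**Step 3: the CV at which 17.2% is passed.** A width of 17.2% corresponds to a design effect of (0.172 / (2 × 2.120))² × 1,394 / 0.25 ≈ 9.18. Solving the formula in Step 2 gives CV ≈ 0.10. For scale, chance (Poisson) variation in monthly births around a mean of 82 would alone give √82 / 82 ≈ 0.11.

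**Step 4: other weights at ICC 0.10.** For a team of size m, the variance of its rate is 0.25 × [ICC + (1 − ICC)/m]. This was averaged over simulated sets of 17 gamma-distributed team sizes with mean 82.

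| CV | Equal weights | Weights m/(1 + (m − 1) × ICC) |
|---|---|---|
| 0.3 | 17.2% | 17.2% |
| 0.5 | 17.4% | 17.3% |
| 0.7 | 17.8% | 17.6% |

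One fixed illustrative set of sizes with a CV of 0.7 gives 18.0% and 17.7%. The excess is thus at most about 0.8 points under these weights.

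**Step 5: less conservative inputs, same method.**

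- At the pilot ICC of 0.007 and p = 0.50, size weights give 7.2%, 7.4% and 7.7% at CVs of 0.3, 0.5 and 0.7. Equal weights give about 7.3%, 7.8% and 9%. ICC-based weights give 7.2%, 7.3% and 7.5%.
- At the unrounded upper limit of 0.094, size weights give 16.7% with equal teams, 17.3% at CV 0.3 and 18.4% at CV 0.5.
- At ICC 0.10 and the pilot return rate of 31.3%, size weights give 17.0% at CV 0.4 and 17.6% at CV 0.5, so the stated figure is passed between those CVs.

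**The case against.** The equal-size calculation is correct, and the section says what its maximum is taken over: the return rate, with 50% as the worst case. It does not claim a maximum over team-size distributions. A reader might infer an arithmetic error from the heading of this point; the documents do not support that.

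The excess also needs two inputs that the article does not give. The first is the CV. The second is the weights: the article says only that there will be weighting if sizes vary, and says it of the intervals per arm, while 17.2% refers to the rate across arms. A reader might infer that the plan has committed itself to size weights for the overall rate. It has not, and under equal or ICC-based weights the excess nearly disappears.

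It is also tempting to ask the article to adopt ICC-based weights as a free gain in precision. That does not hold. Such weights estimate a precision-weighted team average and not the percentage of women, and they need an ICC that the pilot study estimated only loosely. That is a choice about what to estimate, and it belongs in the separate analysis plan that the article announces.

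Finally, the planning ICC is about 14 times the pilot estimate (0.10 / 0.007), there is no hypothesis testing, the progression criteria are deliberately not quantified, and no threshold for the width is set. No decision turns on one or two points.

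All of this stands and limits the point. What remains is that the closing sentence states a maximum without saying that it assumes equal teams, in a plan that elsewhere expects them to differ.

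**Conclusion.** The point holds in a limited form. The 17.2% is correct for 17 equal teams of 82, but it is not a maximum for the plain percentage of women at the plan's own ICC of 0.10 and rate of 50%. There, any team-size CV above about 0.10 exceeds it: by 0.6 points at 0.3 (17.8), 1.8 at 0.5 (19.0) and 3.4 at 0.7 (20.6). These sizes rest on assumed CVs and on size weights, neither of which the article states.

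The effect is minor. A reader might go further and infer that the sample is too small or that the trial's precision is inadequate. The documents do not support that: the widths near the pilot ICC are less than or about half the stated figure, and the article sets no width that must be met. The defect is one planning statement that is worded too strongly.

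**What to change.** In the Sample size section, recompute the width with the design effect 1 + [(1 + CV²) × 82 − 1] × ICC. Take the CV from the monthly bookings per team, which the minimisation needs in any case; they stand in for the births in the sample month. Replace the stated maximum with that figure and its assumptions: ICC 0.10, rate 50%, the CV used, and weights proportional to size. If this is not done, say at least that 17.2% assumes equal team sizes. The choice of weights for the analysis can stay with the statistical analysis plan.

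The cost is a short calculation and a sentence. The downside is that the stated precision becomes slightly less favourable. Recruitment, outcomes and conduct do not change.

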#### Statistical analysis

A separate Statistical Analysis Plan will be produced to provide a comprehensive description of planned statistical analyses. We provide an overall summary of the proposed analysis here. The primary comparison groups are women in clusters allocated to intervention versus women in clusters allocated to standard care. In the first instance, all statistical analyses will be based on the intention to treat principle. Data analysis will be descriptive and mainly focus on confidence interval estimation, with no hypothesis testing. The assessment of missing data is an outcome measure of this feasibility and pilot trial.

We will report numbers contributing and numbers missing for all variables and descriptive statistics for all outcomes. Analysis methods will be chosen according to the data type of the outcome under investigation, in brief:Continuous endpoints (e.g. confidence scores elicited on a range 0**–**32): These data will be summarised using means and standard deviations, by armCategorical (dichotomous) endpoints (e.g. experience of UI in the past 4 weeks): The number of participants and percentages experiencing the event will be summarised by arm

For all total scores and dichotomous feasibility outcomes (e.g. proportion of women returning questionnaires) summary measures and 95% confidence intervals per trial arm will be estimated using a cluster level analysis, the *t*-distribution with df = *K*-1 and appropriate transformation where necessary (and weighting if there is variation in cluster sizes). This approach will appropriately allow for the clustered nature of the trial.

Quantitative data from intervention cluster midwives pre- and post-training session and intervention implementation questionnaires will be summarised using descriptive statistics and where appropriate inferential analysis undertaken using repeated measures statistical tests.

The final dataset will be available to members of the Trial Management and co-applicant group who need access to the data to undertake the final analyses.

Requests for access to data from the APPEAL trial should be addressed to [contact]. Anonymised individual participant data collected during the trial will be available with no end date. All proposals requesting data access will need to specify how the data will be used, and will need the approval of the trial management group prior to data release.

#### Qualitative data

Adherence to implementing the PFME training and fidelity to the intervention will be described through qualitative methods using interviews with midwives who provided care in intervention clusters. Women’s views of support for performing PFME in pregnancy will also be described through qualitative methods using interviews.

Qualitative data in free text responses from intervention cluster midwives pre- and post-training session and intervention implementation questionnaires will be analysed using content analysis.

The interview audio data from midwives and women will be transcribed verbatim. The transcripts will be checked with initial familiarisation process by one researcher who will begin the coding process. A second researcher will independently code a subset of transcripts before coming together to discuss and agree the final coding framework. The principles of the framework method will be used for this process. For each qualitative data set, emerging themes will be charted and data from transcripts summarised under each theme.

A mixed-methods approach will integrate results from each data source [25] affording a fuller picture of the results with ‘triangulation’ occurring at the interpretation stage after each data source has been analysed separately. A summary matrix will be created with an assessment of whether there is agreement, partial agreement, disagreement or ‘silence’ (no data informing that theme) from the differing data sources.

#### Patient and public involvement

Patient and public involvement (PPI) has occurred throughout all phases of APPEAL programme: from developing the original study questions for each of the four Work Packages (including the protocol for the feasibility and pilot cluster trial reported here) to APPEAL logo design.

For the feasibility and pilot cluster trial reported here, the PPI group contributed to the design and choice of resources midwives would provide to women (leaflet, APP card, reminder sticker with APPEAL logo, bag) to remind them to perform their PFME during pregnancy, and how to perform PFME.

Our PPI representatives checked and commented on the participant information sheet and topic guide for the women’s interviews. The PPI group will meet to discuss preliminary trial and process evaluation findings and their views/discussion points used to inform interpretation dissemination of findings.

#### Dissemination

A lay summary of the study will be available on the National Institute for Health Research website. Final results will be publicly available through open-access publication in a peer-reviewed journal and presented at relevant conferences and research meetings. The PPI group will contribute to the dissemination plan.

## Discussion

Urinary incontinence is a widespread and persistent problem following birth, with good evidence that PFME in pregnancy can prevent it, yet few women are advised to perform PFME in pregnancy, and training to enable midwives to support women to manage this aspect of their health at antenatal contacts is not provided. This feasibility and pilot cluster trial was designed to provide evidence of whether a definitive trial of effectiveness could be undertaken.

The trial team will also have to consider other external factors. Following a trial pause due to COVID-19 it became apparent that a future definitive cluster trial of effectiveness may not be possible. This is due to changes to routine care starting to be implemented as part of the NHS England Long-Term Plan to improve women’s pelvic floor health, which will include training of midwives to support women to undertake PFME in pregnancy as well as postnatal access to physiotherapy and multi-disciplinary pelvic health clinics by 2023/2024. NHS England (NHSE) had been expecting APPEAL feasibility and pilot trial findings to inform this plan but early implementation funding provided by NHSE could not be paused. It is expected that new services will be in place across England by 2024. It may therefore be that a full RCT, as was our original aim, will not be possible. However, findings of the APPEAL feasibility and pilot trial will inform and support the NHSE ambition for better perinatal pelvic floor health and will inform services elsewhere internationally.

## Data Availability

Data sharing is not applicable to this article as no datasets were generated or analysed during the current study
